## Methods/design

### Study design and schedule

RAPRASI is a clinical research study for participants with upper gastrointestinal malignancies (without metastatic disease) and who have controlled and stable kidney function. Radiotherapy treatment technique is according to local departmental protocols. Participants are being recruited as they present to the Department of Radiation Oncology, Sir Charles Gairdner Hospital (SCGH) in Perth, Australia, and to the Department of Radiation Oncology, Peter MacCallum Cancer Centre (PMCC) in Melbourne, Australia. The protocol has been approved by both institutional ethics committees. All patients are required to give written informed consent.

In addition to a baseline visit, timed to coincide with participants having a CT scan for the purpose of radiotherapy simulation, participants will have follow-up visits at 4, 12, 26, 52 and 78 weeks subsequent to the first radiotherapy treatment fraction. On each occasion they will undergo: a sequential ^99m^Tc-DMSA SPECT/CT (simultaneous SPECT and CT images), a GFR measurement (^51^Cr-EDTA clearance), a full blood count and assessment of blood urea and electrolytes.

The timing of SPECT/CT scans is intended to reveal i) acute and sub acute changes in total kidney function (GFR measurement) before and following radiotherapy, ii) information on kidney positioning before and following radiotherapy, and iii) the time-dependence of changes in regional kidney function and position (SPECT/CT scans) before and following treatment.

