### Exclusion criteria

– Major co-morbid illnesses that, in the opinion of the investigator, would prevent the patient undergoing planned SPECT/CT scans during the first year following treatment.

– Evidence of metastatic disease.

– Significant loss of bodyweight (>15% weight loss since diagnosis).

– Inadequate bone marrow function to undergo planned therapy.

– Previous drug-induced nephrotoxicity and/or planned treatments that are likely to cause drug-induced nephrotoxicity.

– Previous abdominal radiotherapy.

– Pregnancy or lactation.

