It is anticipated that all participant data will be utilized in the final analysis provided that each participant completes at least the baseline (pre-radiotherapy) and first SPECT/CT scan at 4 weeks post start of radiotherapy. If a participant commences radiotherapy (i.e. completes the baseline SPECT/CT scan) but withdraws consent mid-treatment or is unable to complete any further SPECT/CT scans, then the data for that participant will be excluded from the final analysis.

Data relating to co-morbidities and concurrent treatments, including adjuvant chemotherapy, known to influence kidney toxicity [2], will be extracted from participant notes.

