**Figure 2 F2:**
[figure not shown]
Diagram of the co-registration method.

This subsequent analysis of co-registered dose and image data will be undertaken in several ways:

i. Methods will be developed to assess dose-response correlations as a function of spatial position across each kidney (sampled at varying resolutions). Kidney volumes will be uniformly divided into regions on the three-dimensional (3D) grid defining image and spatially-registered radiation dose. t-tests and Wilcoxon signed-rank tests will be undertaken to determine regions with significantly different mean SPECT-signal intensities between time-points for each study participant. Mixed modelling with repeated measures (and random subject effect) will be conducted across all participant sets to examine the correlation of local radiation dose with SPECT signal changes, generating a map of dose-response change across all kidney volumes. Given a significant correlation, this will be extended to incorporate any revealed patterns of co-morbidity or adjuvant therapy as categorical variables.

ii. Dose-response correlations will then be examined according to structural and functional regions. Analysis i. will be repeated, but with regions defined according to kidney structure, with medulla, renal artery and cortex regions treated independently. This will also involve cross-correlation between these regions to examine inter-play that is likely to arise due to the influence of radiation effects on vascular structures.

iii. Spatio-temporal mathematical models of functional kidney dose-response will be implemented to relate regional kidney irradiation to the primary measure of total kidney function, GFR. These models, including percolation theory [25] and the critical functioning volume model of Rutkowska et al [26], will utilise the 3D radiotherapy dose distribution (both across each kidney and across individual functional regions) to fit model parameters using maximum likelihood estimation (MLE) methods. The statistical assessment of fitting will be made by assessment of parameter confidence intervals, and by undertaking an F-test of the residual sums-of-squares from MLE against that from MLE for a simple linear (single-parameter) dose-response model.

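### Adjustment for co-morbidity and adjuvant therapy should not depend on a significant unadjusted dose–SPECT correlation

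*Protocol article*

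**What the plan says.** The relevant rule is in the protocol article, Methods/design, Data analysis, item i. The model comes first: "Mixed modelling with repeated measures (and random subject effect) will be conducted across all participant sets", its purpose being "to examine the correlation of local radiation dose with SPECT signal changes, generating a map of dose-response change across all kidney volumes". Dose is the only explanatory variable named for it. The next sentence sets the rule for patient factors: "Given a significant correlation, this will be extended to incorporate any revealed patterns of co-morbidity or adjuvant therapy as categorical variables".

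Three other places bear on this.

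- Data collection and quality assurance says that data on co-morbidities and "concurrent treatments, including adjuvant chemotherapy, known to influence kidney toxicity" will be taken from participant notes. The factors are therefore recognised in advance and collected.
- Exclusion criteria rules out previous drug-induced nephrotoxicity and "planned treatments that are likely to cause drug-induced nephrotoxicity".
- Study design and schedule gives the time axis: "participants will have follow-up visits at 4, 12, 26, 52 and 78 weeks subsequent to the first radiotherapy treatment fraction". It also leaves radiotherapy technique to each department.

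**The concern.** The rule has two parts, and both are weak. Adjustment happens only if the unadjusted result is significant, and the factors adjusted for are those whose patterns the data happen to show.

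The study is observational. Kidney dose follows from tumour site, technique and centre, so it may also track chemotherapy or co-morbidity. If such a factor runs against dose, a real dose effect is diluted, the first test may fail, and the adjusted model that would have shown the effect is never fitted. If it runs with dose, the first test may succeed for the wrong reason.

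At stake is the study's first hypothesis, that changes in the SPECT images over time follow the pattern of dose, together with the dose-response map from item i.

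**Working it through.** **The plan's own figure.** The article gives no operating figure for the mixed model. Its only calculation, in Statistical considerations, is a paired t-test: 10% reduction, 20% measurement error, alpha 0.05, power 80%, giving 33 patients, or 10.5% detectable with 30. Taking 20% as the SD of the paired difference, the exact two-sided calculation gives 34 (33 gives 79.5% power) and 10.58% detectable with 30. That agrees closely enough and is not in dispute. It supplies two inputs below: 30 patients and an SD of 20.

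**Assumed inputs, not in the documents.** A binary patient factor is present in 50% of patients. Mean kidney dose differs by 10 Gy between factor groups. The SD of patient-mean dose within a group is 6 Gy and the SD of regional dose within a patient is 10 Gy. The factor shifts SPECT change by 20 points. The patient SD is 10. Region errors are independent. A result is significant if |z| > 1.96.

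**Case A: factor effect constant over time.** The model is y = βD + γc + u + e, where D is regional dose, c the factor, u the random subject effect and e the residual. Rates are the percentage of simulated trials with a significant dose term (1,500 trials per cell; 600 at 200 regions).

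| Regions per patient | β = 0, γ = −20: unadjusted | adjusted | β = −0.3 per Gy, γ = +20: unadjusted | adjusted |
|---|---|---|---|---|
| 2 | 17% | 7% | 7% | 25% |
| 8 | 15% | 5% | 32% | 67% |
| 50 | 8% | 5% | >99% | 100% |
| 200 | 5.5% | 4% | 100% | 100% |

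The reason can be seen by arithmetic. In a regression on patient means alone, the false slope is γ·cov(c, D̄)/var(D̄). Here cov = 10 × 0.25 = 2.5, and var = 10² × 0.25 + 6² + 10²/R = 61 + 100/R, with R the number of regions.

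- R = 2: −20 × 2.5/111 = −0.45 per Gy (simulated −0.446).
- R = 50: −20 × 2.5/63 = −0.79 per Gy (simulated −0.801).

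So the between-patient contrast stays badly biased however many regions there are. The mixed model averages it with the unbiased within-patient contrast, which dominates as regions increase: its simulated false slope falls from −0.236 with 2 regions to −0.024 with 50 and −0.006 with 200.

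**Case B: factor effect growing over the five visits, test on dose-by-time.** The model is y = βDt + γct + u + e with t = 0.2, 0.4, …, 1 and a random intercept only (500 trials per cell).

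| Regions per patient | β = 0, γ = −20: unadjusted | adjusted | β = −0.3, γ = +20: unadjusted | adjusted |
|---|---|---|---|---|
| 2 | 18% | 5% | 6% | 14% |
| 8 | 45% | 5% | 5% | 37% |
| 50 | 97% | 6% | 12% | 99% |

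Here the random intercept does not help, because it cannot absorb a patient-specific trend. The false slope is about γ·cov(c, D)/var(D) = −20 × 2.5/(61 + 100) = −0.31, whatever the number of regions (simulated −0.324, −0.300, −0.298). More regions only shrink the standard error around a wrong value. In the masked scenario the net slope is −0.30 + 0.31 = +0.01, so the low unadjusted power reflects confounding that almost exactly cancels the assumed effect.

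**Precision.** The simulation error at a 5% rate is √(0.05 × 0.95/n): 0.6 points for n = 1,500, 0.9 for 600 and 1.0 for 500. The difference between 5.5% and 4% at 200 regions is therefore not meaningful.

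**The case against.** The strongest reply is that the planned model already handles much of this. Chemotherapy and co-morbidity are patient-level factors, while much of the dose contrast lies inside one patient's kidneys. A second random-intercept simulation with other assumed inputs supports the reply: dose effect −10 per SD, therapy −15, residual SD 20, patient SD 10, dose–therapy correlation 0.6 in size, effects constant over time. When therapy ran against dose, the first test was significant in all trials with 8, 50 or 200 regions, and the unadjusted slopes were −9.2, −9.8 and −9.9. When therapy ran with dose and dose had no effect, false positives were 11%, 6.5% and 6.7%, against 5.3%, 4.5% and 5.9% adjusted. This stands for that setting. It does not cover coarse resolution, and the article plans to examine dose response "as a function of spatial position across each kidney (sampled at varying resolutions"). Nor does it cover factor effects that change over the visits.

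A reader might reduce each patient to one value and infer that most trials would miss the adjusted model (34% significant unadjusted, 59% adjusted) and that a slope reported only after significance would average −13.4 instead of −10. Those figures come from ordinary least squares without regions or a random effect, which is not the model in item i. In the regional simulation above, the adjusted slope after a significant first test averaged −10.0.

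A reader might also infer that an overstated slope passes into the predictive models. The text does not support this. Items iii and iv fit their own parameters by maximum likelihood and carry no such condition.

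Three further replies stand in part. The exclusion of treatments likely to be nephrotoxic narrows the problem, but the article still expects influential adjuvant therapy, and co-morbidity remains. The documents do not say that these factors are related to kidney dose, so confounding is possible, not shown. When the first test is significant, the later adjustment may expose a false result, but nothing does so for a missed one. Covariate detail may be left to a fuller document. The condition on significance, however, is a rule that this article states.

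**Conclusion.** The point holds in a limited form. Item i makes adjustment depend on a significant unadjusted result and on patterns found in the data, for factors the article already recognises and collects. No adjusted analysis is described if the first test fails.

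The effect on the test of the first hypothesis depends on how the model is used. With a constant factor effect and 50 to 200 regions per patient, it is small. It is material with few regions, in between-patient contrasts, and when chemotherapy or co-morbidity effects change over the 78 weeks. Case B further assumes that the test is on dose-by-time, which the article does not state, although its first hypothesis concerns change over time. All rates rest on assumed confounding strength, so they show how the error arises and not how often it would occur here. Items iii and iv are not affected. This is a cheap improvement, of minor to moderate severity.

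**What to change.** Replace the conditional sentence in item i with:

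> The mixed model of SPECT change on local dose will include adjuvant/concurrent chemotherapy (yes/no) and renal-relevant co-morbidity (yes/no), with their interactions with time, as fixed effects from the outset, whatever the unadjusted result. The unadjusted model will be reported alongside, and any further covariate pattern found in the data will be labelled exploratory.

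Chemotherapy is named without a nephrotoxicity qualifier because the exclusion criteria could leave a nephrotoxic-only category almost empty. Separating within-patient from between-patient dose in the same model would also show which contrast carries the result.

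No new data are needed. The cost is a few degrees of freedom among about 30 patients: with linear time, two covariates and their interactions add 2 × 2 = 4 coefficients; with the five visits as categories, 2 × 5 = 10. The covariate list must therefore stay short.

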– Indication of existing and acquired co-morbidities.

– Information on adjuvant treatments.

GFR measurements using the ^51^Cr-EDTA clearance and Digital Imaging and Communication in Medicine (DICOM) formatted SPECT/CT images will be obtained on Siemens Symbia T6 SPECT/CT scanners located in the Department of Nuclear Medicine at SCGH and the Centre for Molecular Imaging at the PMCC. These images involve pre-injection of approximately 185 MBq of ^99m^Tc-DMSA (Radpharm DMS 1987/1), providing 128x128 pixel attenuation-corrected images reconstructed at approximately 5 mm pixel resolution. SPECT images are automatically registered to CT taken on the same device (6 slice helical CT scanner), with image settings sufficient for organ definition and bone matching with minimal radiation dose (typically 130 kV, 80-100 mA, 5 mm slice thickness). SPECT pixel intensity values will be normalised according to calibration images obtained on the scanner during monthly quality-assurance checks. SPECT data will be reconstructed using an ordered subset expectation maximization (OSEM) algorithm incorporating CT attenuation data.

Treatment plan data (images, structures, beam definitions, dose-volume data, and 3D dose distribution) will be exported in DICOM-RT format from the Treatment Planning System. (CMS XiO at SCGH, Varian Eclipse at PeterMac). Digitally reconstructed radiographs (DRRs) will be generated indicating local bony anatomy (upper pelvis, spine, ribs) and the location of kidneys from the planning CT. Variation in kidney position relative to local bony anatomy is of the order of SPECT image resolution [20,21]. Patient localisation will initially be to external marks, with on-line positioning then corrected according to localisation images spatially matched to the DRRs. Localisation images will be obtained either with the Brainlab Exactrac system (6D patient positioning) [22] or the Varian On-Board Imaging system (3D positioning) [23]. Applied patient shifts will be recorded together with localisation images. Where possible, kidney position will be identified on the localisation images for comparison with planned kidney outlines, as per standard departmental practice.

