### Statistical considerations

A target of 30 complete participant datasets has been set based on an assessment of anticipated patient numbers, recruitment and attrition rates, together with a power calculation of the number of datasets required to indicate a statistically significant variation in SPECT image intensity. A clinically significant difference would be a reduction of 20% from baseline to a follow-up imaging study [5]. In order to detect a conservative estimate of a 10% reduction, where the measurement error is 20% we would require a sample size of 33 (using a paired t-test with alpha = 0.05 and power = 80%; detecting 10.5% with 30 patients which is sufficient). With an anticipated 20% non-completion/attrition rate, allowance will be made for up to 40 recruited patients. Given the intensive data analysis required per patient dataset in this study, 30 datasets represents an upper-limit in terms of manageability.

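### In analysis ii, image spill-over and shared dose can by themselves correlate medulla, renal artery and cortex, so the cross-correlation alone cannot show vascular inter-play

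*Protocol article*

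**What the plan says.** The Protocol article, Data analysis, item ii, repeats analysis i with regions set by kidney structure, "with medulla, renal artery and cortex regions treated independently". It adds "cross-correlation between these regions to examine inter-play that is likely to arise due to the influence of radiation effects on vascular structures". Both the statistic and its purpose are therefore stated.

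The model carried over from analysis i is also stated: "Mixed modelling with repeated measures (and random subject effect) will be conducted across all participant sets".

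The imaging is described under Data collection and quality assurance:

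- SPECT: "providing 128x128 pixel attenuation-corrected images reconstructed at approximately 5 mm pixel resolution".
- Reconstruction: "SPECT data will be reconstructed using an ordered subset expectation maximization (OSEM) algorithm incorporating CT attenuation data".
- The CT on the same device has 5 mm slices, "with image settings sufficient for organ definition and bone matching with minimal radiation dose".
- Kidney position: "Variation in kidney position relative to local bony anatomy is of the order of SPECT image resolution".

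The article gives no point-spread width (FWHM). It mentions neither a partial-volume or spill-over correction nor a reference value against which the cross-correlation is to be judged. Under Statistical considerations, "A target of 30 complete participant datasets has been set".

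**The concern.** Cortex, medulla and renal artery adjoin one another, and their thickness is not large compared with SPECT blur. Some of the signal assigned to one region comes from the next, so two regional SPECT changes share a component even when the tissues respond independently. Attenuation correction does not remove this.

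Shared dose works in the same direction. Neighbouring regions tend to receive similar dose. If each responds only to its own dose, their changes still move together across participants, and a raw cross-correlation does not adjust for that.

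Both mechanisms push the correlation upwards, which is also the sign that vascular inter-play would be expected to give. The study could report a vascular effect that is partly or wholly an imaging and dose-pattern artefact.

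**Working it through.** **The plan's own figure.** No figure is stated for analysis ii. The nearest is the sample size of 33 (paired t-test, 10% reduction, 20% error, alpha 0.05, power 80%). The normal approximation gives (1.960 + 0.842)² × (20/10)² = 31.4, so 32; the exact t calculation gives 34. The stated 33 lies between them. This point neither disputes it nor depends on it.

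**Inputs from the article.** About 5 mm pixels, 5 mm CT slices, 30 complete datasets.

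**Assumptions, not in the article.** A slab with 15 mm of medulla between two 10 mm cortex layers that change together; Gaussian blur with FWHM of 5 to 15 mm; medulla uptake u equal to cortex (u = 1) or half of it (u = 0.5); true relative changes in cortex and medulla independent with equal variance; no measurement noise.

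**Formula.** With σ = FWHM/2.355, a layer from a to b contributes Φ((x−a)/σ) − Φ((x−b)/σ) at position x. Averaging over each region gives weights: CC (cortex signal kept in cortex), MC (medulla into cortex), CM (cortex into medulla), MM (medulla kept). The correlation between measured regional changes is then

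r = (CC·CM + u²·MC·MM) / √[(CC² + u²·MC²)(CM² + u²·MM²)].

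| FWHM (mm) | CC | MC | CM | MM | r, u = 0.5 | r, u = 1 |
|---|---|---|---|---|---|---|
| 5 | 0.831 | 0.085 | 0.113 | 0.887 | 0.30 | 0.23 |
| 8 | 0.729 | 0.135 | 0.180 | 0.819 | 0.49 | 0.39 |
| 10 | 0.664 | 0.168 | 0.224 | 0.774 | 0.61 | 0.51 |
| 12 | 0.603 | 0.198 | 0.264 | 0.729 | 0.71 | 0.62 |
| 15 | 0.526 | 0.236 | 0.315 | 0.664 | 0.83 | 0.76 |

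Worked line, 12 mm and u = 0.5:

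- Numerator: 0.603 × 0.264 + 0.25 × 0.198 × 0.729 = 0.159 + 0.036 = 0.195.
- Denominator: √[(0.364 + 0.010)(0.070 + 0.133)] = 0.275.
- r = 0.195/0.275 = 0.71.
- Share of the medulla-region signal that is really cortex: 0.264/(0.264 + 0.5 × 0.729) = 42%.

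**Reference threshold.** With one pair per participant and n = 30, two-sided 5% significance needs |r| above 2.048/√(28 + 2.048²) = 0.36. In the slab, blur alone passes this at 8 mm and above and falls short at 5 mm.

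**Second geometry.** A 3D ellipsoid kidney was also modelled, again by assumption: semi-axes 27 × 25 × 55 mm, cortex 6 to 10 mm, a 6 mm vessel at the hilum, and cortex:medulla:artery uptake from 1:1:1 to 1:0.25:0.1. True changes in the three regions were again independent.

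| FWHM (mm) | Cortex-medulla | Cortex-artery | Medulla-artery |
|---|---|---|---|
| 5 | 0.22-0.53 | 0.21-0.89 | 0.32-0.70 |
| 10 | 0.48-0.83 | 0.63-0.97 | 0.77-0.93 |
| 15 | 0.71-0.94 | 0.84-0.99 | 0.92-0.98 |

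From 8 mm upwards every pair reaches at least 0.38. At 5 mm with equal uptake the range is only 0.21 to 0.34. Pairs involving the artery are the most exposed, because a small structure with low uptake takes most of its measured signal from its neighbours.

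Noise that is independent between regions would lower these values; shared registration or calibration error would raise them. The contribution of shared dose was not quantified, since the article gives no regional doses.

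**The case against.** **Wording.** A reader might infer from "with medulla, renal artery and cortex regions treated independently" that the three signals are assumed statistically independent. The text does not support that. The phrase most naturally means analysed separately, and the next sentence plans to correlate the regions.

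**Pixel size.** A reader might take about 5 mm as the blur. It is a pixel size and does not fix the FWHM. The size of the artefact therefore rests on assumed geometry, blur and uptake, and at the sharpest setting with equal uptake it is modest. This objection stands in full as to size. It does not change the direction, which is positive in every case computed.

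**What is being correlated.** The text could mean relating dose in one region to response in another, rather than SPECT change to SPECT change. It does not settle this. Under that reading spill-over still mixes the responses, and artery dose still tracks cortex dose, so adjustment for local dose is still needed.

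**Position.** The statement on kidney position concerns the kidney relative to bone, and the Data analysis section plans deformable registration on both CT anatomy and SPECT signal. Registration may reduce misalignment, but it does not remove blur.

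**Condensed article.** The full protocol or an analysis plan, neither of which is shown, may contain a correction. For that reason the point is not that a correction is missing. It is that the stated statistic does not, on its own, support its stated purpose.

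**Cortex as response.** Cortex signal is itself blurred by its neighbours, so choosing it as the response reduces the problem without removing it. This also stands.

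**Conclusion.** The point holds in a limited form. Nothing stated in analysis ii separates vascular inter-play from spill-over and shared dose, so inter-play cannot be inferred from the inter-region cross-correlation alone. In the assumed slab, blur alone yields a cortex-medulla r of about 0.2 to 0.3 at 5 mm FWHM and about 0.4 to 0.8 at 8 to 15 mm. These figures illustrate the size and are not estimates for this scanner.

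A reader might go further and conclude that analysis ii cannot be answered at all. The documents do not support that: dose-response region by region remains estimable, though each region's signal is contaminated by its neighbours, and the cross-correlation becomes interpretable once it has a suitable null.

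Nor does the problem run through the whole study. The sample size and analysis i do not depend on it. Analysis iii relates regional dose to GFR, so mixing of regional SPECT signals does not enter it directly. The issue is confined to the interpretation of one secondary analysis, where it is worth correcting before results are read.

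**What to change.** 1. In the mixed model already planned, test inter-play as the effect of renal artery dose, or medulla dose, on cortex (or whole-parenchyma) SPECT change after adjusting for local dose. This works under either reading of the cross-correlation.
2. Report any inter-region SPECT correlation only against a null obtained by blurring independent regional changes with the scanner's measured resolution. Apply the same simulation to a medulla-dose effect on cortex, since medulla signal also spills into cortex.
3. State which quantities are cross-correlated: SPECT change with SPECT change, or dose in one region with response in another.

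Separate medulla and artery SPECT results need not be dropped, but they should carry less weight. No new participants or study scans are needed. The cost is a measurement of scanner resolution, a simulation and some extra modelling. Regional doses are likely to be correlated, so with 30 datasets the adjusted effects may be imprecise. That imprecision would show in the confidence intervals, whereas the raw correlation conceals the difficulty.
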